#### Multivariate analysis

Multivariate analyses will be carried out using regression models with dichotomised union, stability and NDI as dependent variables, and with the secondary outcome parameters as independent variables and covariates. Propensity score analysis will be used to generate a model to predict the treatment received with the baseline variables:

•Patient age (both dichotomised (≤80 and >80 years) and continuous)

•Fracture characteristics (type of fracture)

•Fracture displacement (in mm and direction)

•Severity of osteoporosis in C2

•Facet joint degeneration in C1-C2

•NDI

•MDI

•VAS neck pain

•SF-36

•EQ-5D

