**Methods/Design:**

The trial is an observational study in which eleven centres in five European countries are involved. All patients admitted to one of these centres who meet the selection criteria (≥55 years, acute (<two weeks) type II/III odontoid fracture, no rheumatoid arthritis, no ankylosing spondylitis, no previous treatment for odontoid fracture) are asked to participate. The applied treatment is in accordance with usual care and chosen by the treating surgeon and patient. A cohort of 275 patients will be included. Clinical and radiological follow-up moments are scheduled at 6, 12, 26, 52 and 104 weeks, at which both surgeon and patient will complete Case Record Forms (CRFs). The primary outcome will be a combination of fracture healing and clinical outcome at 52 weeks. Osseous union and fracture stability will be assessed with CT-imaging and dynamic X-ray. Clinical outcome will be scored by the Neck Disability Index (NDI) and correlated to the imaging data. Additionally, predefined subgroup analysis will be carried out (i.e. for patient age and osteoporosis) and prognostic factors will be identified.

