Furthermore, the goal of treatment is still debatable. It is unknown whether or not non-union always leads to complaints in the patient. Consequently, debate remains as to whether the goal of treatment should be osseous union, fracture stability or a favourable clinical outcome. The measurement of these parameters is likewise not uniformly described. The available literature shows higher osseous union rates in surgically compared to conservatively treated patients (66–85% and 28–44%, respectively), but patient selection mechanisms may have profoundly interfered with these outcome percentages. The majority of patients achieved fracture stability regardless of the applied treatment (82-97% in surgically treated patients and 53-79% in conservatively treated patients). There are insufficient data available, especially from direct comparisons, to determine the difference in clinical outcome between surgical and conservative treatment strategies. There is no evidence that clinical outcome correlates better to fracture union than to fracture stability, or that the quality of union, whether it be osseous of fibrous, influences clinical outcome [12].

The goal of this study is to prospectively compare fracture union, fracture stability and NDI improvement at 52 weeks between surgical and conservative treatments in patients over 55 years of age with acute type II and III odontoid fractures. Predefined subgroup analysis may offer prognostic factors that can predict the success of either a surgical or conservative treatment. The influence of age (≥55-80 and ≥80 years) on treatment outcome will particularly be studied. The outcome of this study will yield valuable information enabling more rational decision making in treating the elderly patient population.

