### Sample size

Based on the recent literature review, the estimated possible difference in fracture union between the groups is 41% and in fracture stability this difference is 21% [12]. For both union and stability, however, a smaller difference of 20% would be clinically relevant and the study is powered to assess this difference. For the NDI, a 7.5 point difference (on a 50 point scale) is generally accepted as a minimal clinically important difference with a SD of approximately 10 in various psychometric studies [26-29]. Furthermore, it is expected that the number of patients that will be treated surgically will be twice the number of patients that are treated conservatively (2:1) [14]. Since three primary outcome hypotheses will be tested, the significance level (α) has to be divided by three. Based on the primary outcome parameters, the required sample size, assuming α = 0.05/3 = 0.0167 (two-sided) and β = 0.20 (80% power) and an expected drop out rate of 10%, is 275 for union, 198 for stability and 93 for the NDI. In conclusion, 275 patients will need to be recruited in order to give a reliable conclusion to the comparison of union, stability and clinical outcome between the surgically and conservatively treated groups.

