### Data analysis

Data analysis will be carried out based on the intention-to-treat principle. Cross-over-cases (e.g. surgery after failed conservative treatment) will be analysed among the original treatment group. This will not cause methodological problems because it is two healthcare strategies that are being compared, as opposed to two specific treatments. The reasons for cross-over of patients will be studied and reported. Causes of death will be analysed and a potential relation to the diagnosis and the applied treatment will be studied.

As-treated analysis will additionally be carried out in a sensitivity analysis and prognostic factors for the likeliness of surgery after failed conservative treatment will be studied.

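### The planned regression for fracture stability lists about 13 to 23 parameters against an expected 22 to 68 unstable patients; if fitted jointly by ordinary maximum likelihood, its odds ratios are likely to be biased away from 1

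*Protocol article*

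**What the plan says.** The Multivariate analysis section of the protocol article specifies "regression models with dichotomised union, stability and NDI as dependent variables, and with the secondary outcome parameters as independent variables and covariates". The Secondary outcome section lists the items this refers to:

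- seven questionnaires (MDI, VAS neck pain, SF-36, EQ-5D, DS14, IPQ-K, Likert);
- four radiological items: displacement in mm, direction in five categories, and four-grade scales for osteoporosis and joint degeneration;
- complications and secondary surgery.

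The Multivariate analysis section separately plans a propensity score model.

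Background gives literature stability rates of "82-97% in surgically treated patients and 53-79% in conservatively treated patients". Sample size expects two surgical patients for each conservative one and, with "an expected drop out rate of 10%, is 275 for union, 198 for stability and 93 for the NDI", sizes the study for the three two-group comparisons only.

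The regression results are meant to be used. The abstract says that "prognostic factors will be identified", and the Discussion aims to find factors that predict treatment success in individual patients.

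**The concern.** The information in a binary regression is governed by the rarer outcome, not by the number of patients. Most patients are expected to reach stability, so the rarer outcome is instability. The named covariate set looks long for the number of unstable patients that the protocol's own figures allow.

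When maximum-likelihood logistic regression has very few events per parameter, its odds ratios are biased away from 1 on average. Prognostic factors are a declared aim. Treatment is also chosen by surgeon and patient, so readers are likely to give weight to adjusted estimates. An inflated adjusted odds ratio, or a chance predictor reported as prognostic, could therefore influence how the study is read.

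**Working it through.** **1. The plan's own sample sizes.** They are two-group calculations with α = 0.05/3 two-sided, 80% power and a 2:1 ratio.
- NDI: smaller group = (2.394 + 0.842)² × 10² × 1.5 / 7.5² = 27.9, so 28. The total is 84, and 84 × 1.1 = 92.4, so 93 (stated 93).
- Stability, taking 89.5% (midpoint of the surgical range) v 69.5%: smaller group 59, total 177, and 177/0.9 = 197 (stated 198).
- Union: no base rate is stated. An assumed 78% v 58% gives 246, and 246/0.9 = 274 (stated 275).

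None of these sizes a regression model.

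**2. Expected unstable patients.** Evaluable: 275 × 0.9 = 247.5, that is 165 surgical and 82.5 conservative. Unstable = 165 × (1 − p_surg) + 82.5 × (1 − p_cons).
- Both ranges at the top (97%, 79%): 4.95 + 17.3 = 22
- Midpoints (89.5%, 66%): 17.3 + 28.1 = 45
- Both at the bottom (82%, 53%): 29.7 + 38.8 = 68

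**3. Parameters (inferred; the protocol gives no count).**
- Lowest: one linear term per item, 7 + 4 + 2 = 13, or 14 with treatment.
- Highest: questionnaires 8–9 (two SF-36 summaries, one or two DS14 terms), radiology 1 + 4 + 3 + 3 = 11, complications and secondary surgery 2, treatment 1, total 22–23. Eight SF-36 domains would raise this further.

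**4. Events per parameter.** From 22/23 = 0.96 to 68/13 = 5.2.

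Restricting the listed items to those with pre-treatment values (MDI, VAS, SF-36, EQ-5D and the radiological items) leaves 16 terms, or 12 with ordinal grades. That gives 22/16 = 1.4 to 68/12 = 5.7, so the shortage is separate from the question of post-treatment covariates.

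**5. Size of the bias.** Simulated joint maximum-likelihood fits: 247 patients, treatment plus pure-noise covariates, geometric-mean odds ratio for stability, surgical v conservative. Ranges are over repeated simulations.

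| Unstable | True OR | 13–14 parameters | 19–23 parameters |
|---|---|---|---|
| 68 | 4.0 | 4.3–4.5 | 4.6–5.0 |
| 45 | 4.4 | 4.9–5.1 | 5.1–5.6 |
| 22 | 8.6 | 11.3–11.9 | 13–17 |

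- 68 events: 4.3/4.0 = 1.07 to 4.9/4.0 = 1.23 (the highest run, 5.0, gives 1.25).
- 45 events: 4.9/4.4 = 1.11 to 5.6/4.4 = 1.27.
- 22 events: 11.3/8.6 = 1.31 to 17/8.6 = 1.98.

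A second simulation used correlated predictors (correlation 0.3, assumed) and one real predictor with OR 1.8 per SD (assumed). With 13–23 parameters it estimated that predictor on average at 1.89–1.97 (68 events), 1.90–2.01 (45) and 1.98–2.27 (22).

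**6. Chance predictors at 0.05.** At least one noise term was significant in about 43–53% of models with 13–14 parameters and 61–76% with 19–23. With unlimited data, 12 noise terms would give 1 − 0.95¹² = 46% and 18 would give 1 − 0.95¹⁸ = 60%. The error per noise term was about 5.3–7.7% against 5%.

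**7. Union for comparison.** Background gives union in 66–85% (surgical) and 28–44% (conservative). Non-unions: 165 × 0.15 + 82.5 × 0.56 = 71 to 165 × 0.34 + 82.5 × 0.72 = 115.5. That is 71/23 = 3.1 to 115/13 = 8.8 per parameter. No response rate is given for dichotomised NDI, so that model cannot be checked.

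**The case against.** The strongest reply is that much of this model is inferred. The protocol speaks of regression models in the plural and states no joint entry, coding, selection or estimation method, which an article may leave to a fuller document. Treatment is not named as a regressor in that sentence, and the treatment comparison has its own primary tests and a propensity score. All of that stands, so the point has to be conditional on joint entry. But the outcome scale and the covariate set are stated. Joint entry is the natural meaning of a multivariate regression, the most favourable coding still leaves at most about five events per parameter, and selecting from the same candidates would not remove the problem.

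A reader might also infer more than the documents support:

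- **That the plan fixes 19–23 parameters.** It fixes a list; 13–14 is an equally possible count.
- **That large inflation is certain.** The large figures need both stability rates at the top of their ranges. Some of the bias there is not due to overloading: with only three covariates the estimate was already 9.7 against 8.6.
- **That few events cause the chance predictors.** Most come from the number of terms tested. Sparse data add only a few percentage points, and penalised fitting of the Firth type would not remove them.
- **That the planned study of predictors of secondary surgery is shown to be overloaded.** The Data analysis section says only that "prognostic factors for the likeliness of surgery after failed conservative treatment will be studied". It names no model or predictor, and the protocol gives no rate of secondary surgery, so no count can be derived.

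**Conclusion.** The point holds in conditional form. The protocol names a covariate set for the stability regression that its own expected data cannot support: roughly 1–5 events per parameter under any reasonable coding. If the terms are entered jointly by ordinary maximum likelihood, odds ratios are likely to be biased away from 1. For the treatment odds ratio the bias is modest at 68 unstable patients (about 7–23%) and severe only at 22 (about 30–100%). About half to three-quarters of such models would show at least one chance predictor, mainly through multiplicity.

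This rests on the literature stability rates in Background, the expected 2:1 split, exactly 10% loss, and an inferred parameter count. Greater loss, for example through deaths in this age group, would lower the event count. Union is less affected (about 71–115 non-unions), and the primary χ² and t-tests are unaffected. The matter should be corrected because prognostic factors are a stated aim, but it concerns a supporting analysis and not the main conclusion.

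**What to change.** Amend the Multivariate analysis section as follows.

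(a) **Treatment effect.** Estimate the adjusted effect on stability from treatment plus the propensity score already planned, not from the regression on all secondary outcome parameters. Firth's penalised likelihood matters only if events fall near the low end. In simulation at 68, 45 and 22 events, three-covariate maximum likelihood gave 4.1, 4.7 and 9.7 against true values of 4.0, 4.4 and 8.6. Firth fitting, even with 19 parameters, gave 4.0, 4.5 and 8.3.

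(b) **Prognostic factors.** Prespecify a short set of pre-treatment variables sized to the expected events. As a guide, 22–68 events would carry about 2–6 parameters at ten events each or 4–13 at five; both thresholds are assumptions, not protocol figures. Enter osteoporosis and degeneration grade as single ordinal terms, fit with shrinkage (for example ridge), report optimism-corrected performance, and label the findings exploratory.

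This changes analysis wording only and needs no extra patients or data. The downside is that fewer predictors can be examined, and the reported odds ratios and discrimination will be smaller.

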### Primary outcome

The primary outcomes are fracture healing and clinical outcome at 52 weeks after the start of treatment:

•Fracture healing will be scored by assessing union (union or non-union) and stability (stable or unstable).

o Union will be defined by evidence of bone trabeculae crossing the fracture site and absence of sclerotic borders adjacent to the fracture site, assessed using computed tomography (CT).

o Fracture stability will be assessed using upright cervical dynamic X-rays in lateral projection. A maximum of 2 mm movement at the fracture site is considered stable, over 2 mm movement at the fracture site is considered unstable [15].

•Clinical outcome; scored by calculation of the improvement compared to baseline in the Neck Disability Index (NDI) [16] score at 52 weeks after start of treatment. The NDI is a widely applied instrument to assess neck pain complaints. It was derived from the Oswestry index for back pain and the Pain Disability Index.

In the sample size calculation, the significance level was adjusted for the multiple primary outcome measures.

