#### Univariate analysis

Univariate analysis will be carried out using χ^2^-tests for dichotomised outcomes and T-tests for continuous outcomes. Intention-to-treat analysis will be used for cases that crossed over to other interventions.

•Primary analysis

The χ^2^-test will be used to test for differences between groups on union and stability at 52 weeks (α = 0.0167). T-test will be used to test for differences between groups on NDI improvement at 52 weeks (α = 0.0167).

•Secondary analysis

The χ^2^-test will be used to analyse the difference in dichotomised NDI. NDI will be dichotomised using the criterium of the minimal clinically important change (improvement) of 7.5 points out of 50. The relation between radiological parameters (union and stability) and NDI will be analysed by comparing the average NDI improvement for patients that acquired union/stability with those that did not.

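### The confirmatory NDI test is an unadjusted change-score t-test in a non-randomised comparison, and no baseline-adjusted analysis of continuous NDI is specified

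*Protocol article*

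**What the plan says.** Under Primary outcome, the protocol article defines clinical outcome as the improvement in NDI from baseline to 52 weeks. Under Univariate analysis (primary analysis) it fixes the test: "T-test will be used to test for differences between groups on NDI improvement at 52 weeks", at α = 0.0167. No covariate is named.

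The secondary analysis adds a χ² test of a responder version: "NDI will be dichotomised using the criterium of the minimal clinically important change (improvement) of 7.5 points out of 50". It also addresses whether bone healing matters for function: "The relation between radiological parameters (union and stability) and NDI will be analysed by comparing the average NDI improvement" between patients with and without union or stability. No adjustment is stated there either.

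Under Multivariate analysis, the adjusted models are "regression models with dichotomised union, stability and NDI as dependent variables", "with the secondary outcome parameters as independent variables and covariates". NDI is not in the Secondary outcome list, so baseline NDI is not among the covariates named for these models. It appears only in the next sentence: "Propensity score analysis will be used to generate a model to predict the treatment received with the baseline variables". The list that follows includes age, fracture features, NDI, VAS neck pain and other questionnaires. The article does not say how that score enters any outcome analysis.

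The Treatment section makes the choice of strategy a shared decision of surgeon and patient. The Background names age, pain, medical condition and neurological deficits among the grounds for that choice.

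**The concern.** In a randomised trial, an unadjusted t-test on change is less efficient than a baseline-adjusted model but unbiased. Here the groups are formed by clinical choice, and the protocol expects baseline NDI, pain and age to predict that choice. The group with worse NDI at the start has more room to improve and, if baseline and follow-up are imperfectly correlated, will on average show more improvement for that reason alone. The confirmatory test does not condition on any of this.

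The adjusted model that is specified works on a different outcome scale. Its estimate is a contrast in the 7.5-point responder rate, so it cannot be set beside the t-test to show how far adjustment moves the mean difference. In the phrase about dichotomised outcomes, the word must apply to NDI: union and stability are already binary, and the responder cut is defined just before.

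The comparison of NDI improvement by union or stability has a similar weakness. The Background reports union of 66–85% after surgery and 28–44% after conservative treatment, so a crude comparison by union status is partly a comparison of treatments.

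**Working it through.** **1. The plan's own NDI sample size.** Inputs from Sample size: difference 7.5, SD 10, α = 0.05/3 two-sided, power 80%, 2:1 allocation, 10% dropout.

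- Smaller group: n = (1 + 1/2) × (2.394 + 0.842)² × (10/7.5)² = 27.9, so 28. The larger group is 56 and the total is 84.
- With dropout: 84/0.9 = 93.3, so 94; or 84 × 1.1 = 92.4, so 93.

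The stated 93 reproduces.

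**2. Power at the planned size.** 275 × 0.9 ≈ 247 evaluable, about 165 and 82. For a true 7.5-point difference:

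- The t-test on change with SD 10 has 99.9% power.
- The article does not say whether SD 10 refers to a single score or to change. If it is a single score, the change SD is 10 × √[2(1−ρ)], which is 12.65 at an assumed ρ = 0.2. Power is then still 97.7%.
- NDI cut at 7.5 points has about 86% to 98% power, for an assumed conservative-group mean improvement of 0 to 15 points and change SD 10.

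Union drives the 275, so NDI has power to spare.

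**3. Gap between the two estimates.** Let D be the baseline difference between groups and b the slope of 52-week NDI on baseline within groups. The change-score contrast and the baseline-adjusted contrast differ by (1−b) × D. With equal SDs at both times, b = ρ. The article gives neither ρ nor D; both are assumptions here, with D = 5 points.

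| Assumed ρ | Gap (1−ρ) × 5 | Share of 7.5 points |
|---|---|---|
| 0.2 | 4.0 | 53% |
| 0.5 | 2.5 | 33% |
| 0.8 | 1.0 | 13% |

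For scale, with change SD 10 the standard error of the t-test contrast is 10 × √(1/165 + 1/82) = 1.35. The gaps are therefore 3.0, 1.9 and 0.7 standard errors, against a critical value of about 2.39.

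**4. Sensitivity to the equal-SD assumption.** If the 52-week SD is 1.5 times the baseline SD and ρ = 0.5, then b = 0.75 and the gap is 0.25 × 5 = 1.25 points, not 2.5.

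**5. Precision.** With equal SDs and balanced baselines, the ratio of adjusted to change-score variance is (1−ρ²)/[2(1−ρ)] = (1+ρ)/2, or 0.60, 0.75 and 0.90 at ρ = 0.2, 0.5 and 0.8. A 5-point imbalance (half of an assumed score SD of 10) with 2:1 groups multiplies the adjusted variance by 1 + (2/3)(1/3)(0.5)² = 1.056. At ρ = 0.5 the ratio becomes 0.75 × 1.056 = 0.79, so the saving falls from 25% to about 21%.

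**The case against.** Four objections carry weight.

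- **Propensity score.** A reader might infer that continuous NDI will never receive a baseline-adjusted analysis. The article does not support that. The propensity model includes baseline NDI, and its use is left open, so a propensity-adjusted analysis of continuous NDI may sit in a fuller document. What stands is that none is specified, while the confirmatory test is fixed as unadjusted.
- **Power.** A reader might infer that change scores or dichotomising leave NDI underpowered. At the protocol's own 7.5 points they do not. A wide contrast (about 71% continuous against 38–48% dichotomised) appears only for a true effect of 4 points, roughly half the stated minimal important difference. The dichotomised test is also secondary; the confirmatory one is already continuous.
- **Gap or bias.** (1−ρ) × imbalance is the distance between two estimates. It is bias in the t-test only if the baseline-conditional model is the right one. In non-randomised groups with stable baseline differences, the adjusted estimate can be the biased one (Lord's paradox). This stands, and it limits the table above to a conditional statement.
- **Union or stability against NDI.** This is a secondary analysis of an association, and the Background says the effect of treatment on clinical outcome is not known. It is therefore too strong to say that treatment and age determine both sides. They are plausible confounders, which is enough reason to adjust.

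**Conclusion.** The point holds on validity, not on power. The article fixes an unadjusted t-test on change as the confirmatory NDI analysis in a comparison where it expects baseline NDI, pain and age to predict treatment. It puts NDI into a regression only after dichotomising it. Under an assumed 5-point imbalance and equal SDs, the choice of analysis moves the NDI estimate by 1.0 to 4.0 points for assumed ρ of 0.8 to 0.2, that is 13% to 53% of the 7.5-point threshold. The shift scales with the imbalance and shrinks if the 52-week SD is larger than the baseline SD. It is bias in the t-test if the baseline-conditional model is correct. The precision gain from adjustment is real but secondary, because the t-test has 99.9% power for 7.5 points with change SD 10. The change should be made, but this does not threaten the size or feasibility of the study.

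**What to change.** 1. Make the primary NDI analysis a linear regression of 52-week NDI on treatment strategy, adjusted for baseline NDI and the baseline variables listed under Multivariate analysis, or for the propensity score built from them. Keep α = 0.0167. Regressing improvement on the same terms gives the same treatment coefficient with the sign reversed, so the endpoint definition can stay.
2. State how the propensity score enters the NDI analysis.
3. Keep the raw t-test and the 7.5-point responder analysis as supportive.
4. Adjust the union or stability comparison of NDI improvement for treatment, age and baseline NDI.

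The cost is wording: Table 3 already schedules NDI at baseline and at 52 weeks. There is a small downside. The adjusted estimate replaces the raw change contrast as the reported result, so the choice needs a sentence of justification. Baseline adjustment also does not remove unmeasured confounding by indication, and the report should say so.

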### Follow-up period

Patients will be seen by the treating surgeon five times for radiological and/or clinical follow-up visits; at 6, 12, 26, 52 and 104 weeks after the start of treatment. In addition to usual patient care, patients will be sent questionnaires (CRFs) to complete at home prior to each follow-up visit (Table 3). On no occasion will patients see the results of earlier assessments. After the last follow-up visit at 104 weeks the patient’s participation in the study ends.

**Table 3 T3:** Data collection and outcome measures

	**Baseline**	**Immediately after start of treatment**	**Weeks of follow-up**				
			**6**	**12**	**26**	**52**	**104**
General status and fracture assessment	**X**						
Demographic data	**X**		**X**	**X**	**X**	**X**	**X**
NDI, MDI, VAS neck pain, SF-36, EQ-5D	**X**	**X***	**X**	**X**	**X**	**X**	**X**
DS14, IPQ-K, Likert			**X**	**X**	**X**	**X**	**X**
Complications of surgery		**X****	**X****	**X****	**X****	**X****	**X****
Secondary surgery			**X****	**X****	**X****	**X****	**X****
Dynamic X-ray					**X**	**X**	**X**
CT-Cervical spine	**X**			**X**	**X****	**X**	

*In case of surgical treatment only.

**When indicated.

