#### Clinical

•Myelopathy Disability Index (MDI) [17]: The MDI is a functional scoring system for cervical myelopathy that was originally designed for patients with rheumatoid arthritis. It consists of a selection of questions from the Standford Health Assessment Questionnaire.

•Visual Analogue Scale (VAS) for neck pain [18,19]: The VAS neck pain score indicates the intensity of experienced neck pain by drawing a mark on a 100 mm line. 0 mm symbolises ‘no pain’ , 100 mm symbolises ‘pain as worse as it could possibly be’.

•Short Form-36 (SF-36) [20,21]: The SF-36 is a generic health survey consisting of 36 questions. It consists of eight domains: physical functioning, physical restrictions, emotional restrictions, social functioning, somatic pain, general mental health, vitality and general health perception. It results in physical and mental health summary measures and a health utility index.

•EuroQol 5 Dimensions (EQ-5D) [22]: The EQ-5D is a tool to measure health outcome. It yields a descriptive profile and single index value for the patient’s health status.

•Type D Scale 14 (DS14) [23]: The DS14 is a standard assessment of negative affectivity, social inhibition, and Type D personality.

•Illness Perception Questionnaire-K (IPQ-K) [24]: The IPQ-K is a brief illness perception questionnaire, using a nine-item scale to rapidly assess the cognitive and emotional representations of the patient’s illness.

•Likert scale on recovery: The Likert scale used for this study is a seven-point scale on the patient’s perceived recovery from complaints and neck pain.

Not all of these questionnaires were already validated in the native languages of all countries involved in this trial. Therefore, prior to the start of the study they were validated by a process of bilateral translation. A native speaker of the target language who was also fluent in English first translated the questionnaire into the target language. A native speaker of English who also spoke the target language and was blinded to the original text then translated the text back into English. The original text and the back translated text were then compared at a consensus meeting. If the meaning of the two texts was agreed to be identical, the question was assumed to be adequately translated. Possible differences were discussed. More extensive options for transcultural adaptation of questionnaires were not considered feasible or necessary in the context of this trial.

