#### General

•Complications: Complications resulting from the application of the different treatments will be monitored to identify potential differences in the occurrence or severity of complications between treatments.

•Re-interventions/Secondary surgery: One of the goals of the conservative treatment policy is to avoid surgery while still achieving fracture healing and a favourable clinical outcome. The rate of secondary surgery is hence an indication of the success or failure of this policy. Secondary interventions and the cause/motivation for its application will therefore be monitored.

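### The outcome regressions take the secondary outcomes as covariates without limiting them to pre-treatment values, and several exist only after treatment has started

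*Protocol article*

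**What the plan says.** The Multivariate analysis section of the protocol article plans "regression models with dichotomised union, stability and NDI as dependent variables", and completes the specification "with the secondary outcome parameters as independent variables and covariates". It neither gives a time point for these covariates nor names treatment group as a term.

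The next sentence turns to a different model: "Propensity score analysis will be used to generate a model to predict the treatment received with the baseline variables". The list that follows (age, fracture type, displacement, osteoporosis, facet joint degeneration, NDI, MDI, VAS, SF-36, EQ-5D) belongs to that model.

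The secondary outcome parameters are set out under the subheadings Clinical, Radiological and General. They include "Likert scale on recovery", complications ("Complications resulting from the application of the different treatments will be monitored") and secondary surgery, of which the article says "The rate of secondary surgery is hence an indication of the success or failure of this policy". Table 3 under Follow-up period gives the measurement times. The row "NDI, MDI, VAS neck pain, SF-36, EQ-5D" is marked at baseline and at all follow-up visits. The row "DS14, IPQ-K, Likert" is marked only from week 6.

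**The concern.** A variable that treatment can change should not be a covariate in a model meant to isolate the effect of treatment. If the effect runs partly through that variable, adjustment removes that part. If the variable and the outcome also share an unmeasured cause, such as frailty, adjustment creates a further association between treatment and outcome that is not causal.

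This matters here because treatment is chosen by surgeon and patient. The primary tests are unadjusted, so readers will look to the adjusted analyses to judge confounding, and this section gives the only regression on outcomes that the article describes.

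Two of the article's own aims also pull against the covariate rule. The Data analysis section compares two care strategies by intention to treat and keeps cross-over cases in their original group. Adjusting for secondary surgery would condition on part of what the strategy produces. The Abstract, Background and Discussion promise prognostic factors, and the Discussion speaks of predicting treatment success in individual patients. A variable first known weeks after the treatment decision cannot serve that purpose.

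**Working it through.** The point concerns model specification, and the plan gives no figure to reproduce. The check sets the covariate rule against the list of secondary outcomes and the schedule in Table 3.

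| Secondary outcome parameter | When recorded (Table 3) | Usable as a pre-treatment covariate? |
|---|---|---|
| Complications | From immediately after start of treatment, when indicated | No |
| Secondary surgery | From week 6, when indicated | No |
| Likert recovery | From week 6 | No |
| IPQ-K | From week 6 | Not as scheduled |
| DS14 | From week 6 | Not as scheduled, though it measures personality and may be little affected |
| MDI, VAS, SF-36, EQ-5D | Baseline and every follow-up | Yes at baseline, no at follow-up; the regression sentence does not say which |
| Displacement, osteoporosis grade, joint degeneration | No row of their own; CT at baseline and later | Yes at baseline |

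A reading under which every covariate is a baseline value is therefore impossible for the first five rows. For the sixth it is possible but not stated.

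**What conditioning can do (illustration on assumed values).** Only the 7.5-point NDI difference, the SD of about 10 and the 2:1 split come from the Sample size section. Everything else is assumed. NDI improvement is treated as continuous for simplicity, although the planned model dichotomises it.

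Let T be treatment and M a follow-up covariate with unit variance within groups, shifted by 0.75 SD by treatment. Let s be the share of the effect that passes through M:

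- Y = 7.5(1 − s)·T + 10s·M + error
- Total effect = 7.5(1 − s) + 10s × 0.75 = 7.5 for every s
- Coefficient of T after adjusting for M = 7.5(1 − s)

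Now add an unmeasured patient factor U (unit variance, independent of T) with assumed weights 0.6 on M and 5 on Y. Within treatment groups the covariance of M with 5U is 0.6 × 5 = 3, and the variance of M is 0.36 + 0.64 = 1. M therefore takes up an extra slope of 3, and the coefficient of T loses 3 × 0.75 = 2.25:

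- Coefficient of T after adjusting for M = 7.5(1 − s) − 2.25

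| s | Unadjusted | Adjusted, no shared cause | Adjusted, shared cause |
|---|---|---|---|
| 0 | 7.5 | 7.5 | 5.25 |
| 0.25 | 7.5 | 5.6 | 3.4 |
| 0.50 | 7.5 | 3.75 | 1.5 |
| 0.75 | 7.5 | 1.9 | −0.4 |
| 1.00 | 7.5 | 0 | −2.25 |

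A simulated linear regression with 400,000 patients agrees to within sampling error (with the shared cause: 5.21, 3.34, 1.49, −0.37, −2.25). With the shared cause the estimate is wrong even when nothing is mediated, and the sign reverses once 7.5(1 − s) < 2.25, that is s > 0.7.

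**The case against.** **The primary analysis is elsewhere.** The treatment comparison that decides the trial is the chi-square and t-tests at α = 0.0167, which use no covariates. This stands. A reader might infer that the main result is biased by the covariate rule; the Univariate analysis section does not support that.

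**Treatment is not named in these models.** They may be meant only to find prognostic factors, and then there is no treatment coefficient to distort. This stands as a limit on the first half of the point. It does not rescue the sentence, because post-treatment variables are no better as predictors available at the time of decision.

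**Baseline-only adjustment is already planned.** The propensity model is built on baseline variables and excludes complications, secondary surgery, Likert, DS14 and IPQ-K. This also stands, so it would be wrong to say that the plan has no sound tool against treatment selection. But the word baseline governs that model alone and does not carry back to the outcome regressions.

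**Not every secondary outcome is a consequence of treatment.** This is correct. Osteoporosis grade, joint degeneration, initial displacement and the baseline MDI, VAS, SF-36 and EQ-5D are legitimate covariates. A blanket charge against all secondary parameters would be too strong.

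**A condensed article may leave covariate timing to a fuller plan.** For the four scales measured at baseline and follow-up, that is a fair defence, and the fault there is ambiguity. For variables that have no pre-treatment value, the article states a rule that no later detail on timing can repair.

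**Conclusion.** The point holds in limited form. The covariate rule is wrong for complications, secondary surgery and Likert recovery, and for any follow-up value of the other scales. It is doubtful for IPQ-K and DS14 as scheduled, and unclear for MDI, VAS, SF-36 and EQ-5D. If treatment is in the model, its adjusted effect is not interpretable as an effect of the strategy. If it is not, the models cannot deliver predictors for use when treatment is chosen.

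The size is not derivable from the document, which gives no correlations between the instruments and no mediation shares. The range from 7.5 to −2.25 shows what is possible on the stated assumptions and is not a forecast.

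A reader might want a sharper figure. Suppose the whole effect runs through one disability construct, shifted by 0.75 SD, that accounts for 70% of the variance of the NDI and of three other 52-week scores. The NDI effect is then 0.75 × √0.7 × 10 = 6.3 points. Entering the three scores together divides it by 1 + 3 × (0.7/0.3) = 8, leaving 0.8. That is an extreme built into the assumptions, not a property of this plan. Nor does the document support saying that the bias usually runs towards no difference: attenuation is common, but the sign can also reverse.

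**What to change.** Replace the covariate phrase in the Multivariate analysis section so that the outcome models contain treatment group and pre-treatment variables only: age, fracture type, baseline displacement, osteoporosis grade, joint degeneration, and baseline NDI, MDI, VAS, SF-36 and EQ-5D.

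Remove complications, secondary surgery, Likert recovery, IPQ-K and all follow-up scores as covariates, and analyse them as outcomes in their own right. If their relation to union, stability or NDI is of interest, declare a separate association or mediation analysis. Use DS14 only with a stated justification that it is a stable trait despite its first measurement at week 6.

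The same edit should say how the propensity score enters the outcome comparison.

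The cost is a change of wording, with no new data and no extra patients. It should be made before outcome data are analysed, so that the covariates are not seen to have been chosen after the results.
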